#### **10.4.3. Qualitative and economic sub-studies**

Qualitative sub-studies will recruit participants being investigated for TB having reported prolonged cough to the TB ACF outreach team or primary care facilities.

Approximately 60 serial in-depth interviews will be carried out with purposively selected participants attending routine TB testing services (Appendix 4.1a&b Consent forms, Appendix 4.6a&b participant information sheets and Appendix 4.8 topic guide). Interviews will explore motivations for health-seeking, and the social and economic consequences of TB investigations and diagnosis.

In addition, approximately 20 health worker will be interviewed to probe their understanding of TB and TB testing practices (Appendix 4.2a&b Consent forms, Appendix 4.7a&b participant information sheets and Appendix 4.9 topic guide).

### **10.5. Enhanced surveillance of TB in Blantyre District**

#### **10.5.1. Electronic TB database**

A tablet-based Electronic TB database, established in 2011 and maintained jointly by Blantyre District Health Office and MLW will be continued (and expanded to include Chiradzulu District Hospital) in order to allow subdistrict TB notification rates to be monitored. All registering patients are interviewed by the District TB Officers, and have a sputum taken for TB microscopy and culture, place of residence identified through a satellite map application, and a questionnaire including all data points required by the National TB Programme reporting system, including HIV status.

Electronic records do not include patient names: patients are managed using paper-based logs that act as the source-documents for the electronic database.

## **10.6. Laboratory methods**

### **10.6.1. ACF sputum specimens**

Smears will be made directly from sputum, dried, stained with Auramine-O and examined under fluorescence microscopy in a quality-assured laboratory. All positive slides and one in ten negative slides will be reread by a second reader in the central MLW/COM laboratory. Positive slides will then be confirmed with ZN staining and graded for positivity according to WHO guidelines.

### **10.6.2. TB sputum culture**

Confirmatory sputum specimens from ACF participants found to be smear positive, all routinely registering TB patients in urban Blantyre, and Prevalence Survey participants qualifying for bacteriological investigation will be processed for culture in Mycobacterial Growth Indicator Tubes, with the residual stored at -20°C in case of contamination.

In the case of contaminated cultures, the stored specimen will be retrieved and recultured after repeat decontamination. Species identification will use MBP 64 lateral flow assays, microscopic cording, and if either of these two are negative, colony morphology, temperature and inhibition by PNB. These tests will be performed in the MLW/COM and laboratory.

Standard Operating Procedures are maintained by the MLW/COM laboratory

### **10.6.3. Storage of specimens**

*M. tuberculosis* isolates will be stored for genotyping. No other specimen storage is anticipated.

DNA extraction from culture positive *Mtb* isolates will be performed in the MLW/COM laboratory by trained technicians. DNA isolates will be shipped to TGen, Arizona, USA under a material transfer agreement, where they will undergo whole genome sequencing for genomic epidemiology and TB transmission sub-studies (detailed above).

### **10.6.4. Laboratory Safety**

Staff training will be given to all employees given regarding universal precautions and avoidance of needle-stick injuries. A policy for needle-stick injuries is in place.

The study Laboratory is a restricted access Category 2 and 3 facility with a quality management system in place, with regular external audit of laboratory procedures.

Sputum specimens handled in the field are unlikely to pose a major hazard, due to natural ventilation and the low concentration of mycobacteria in unprocessed specimens. Nonetheless, safety training will be given to all employees and universal precautions will be used to minimise the hazard of acquiring TB or other respiratory pathogens.

## **10.7. Discontinuation/Withdrawal of Participants**

Each participant has the right to withdraw from the trial at any time. In addition, the Investigator may discontinue a participant from the trial at any time if the Investigator considers it necessary for any reason including ineligibility (either arising during the trial or

retrospectively having been overlooked at screening), significant protocol deviation or withdrawal of consent. The reason for withdrawal will be recorded in the CRF.

#### **10.8. Definition of End of Trial**

The trial will be considered closed following the completion of follow up of the last participant, and once all follow-up and laboratory reports have been received. The trial may be terminated early by the TSC, regulatory authorities or the funders, for example if interim analysis shows an unacceptably high mortality in the intervention arm, as defined in the analysis plan.

## **11. DATA COLLECTION AND MANAGEMENT**

### **11.1. Data management**

Data will be managed at the project offices in MLW. Data analysis will be carried out in-house in collaboration with LSHTM statisticians.

Data collection and entry will be as detailed in the trial SOPs. All data will be entered into Databases, using a combination of Electronic Data Capture onto tablets, and Optical Character Recognition (OCR) of paper forms, with validity checks before scanning, and a protocol for verification of scanned records.

Inconsistencies will be investigated and resolved. ACF and routine health system data will be analysed on completion of each respective stage of the study and for each round of intervention, with the aim being to have all data verified, double entered, checked and resolved according to the data analysis plan. The final analyses will then use the combined study data.

Access to the final data set will be limited to the Trial Coordinator, Statistician, Data Manager, and Principal Investigator.

### **11.2. Data capture forms and questionnaires**

A full set of case-report forms (CRF)s is provided in the Appendices

### **11.3. Patient confidentiality**

The trial staff will ensure that participants anonymity is maintained.

Participants will be identified only by a unique study identifier on the data capture tools and any electronic database. All documents will be stored securely and only accessible by trial staff and authorised personnel. The trial will comply with the Data Protection Act, which requires data to be anonymised as soon as it is practical to do so.

### **11.4. Data security**

Hard copies of data and study documentation will be kept in locked offices, and long-term storage will be in locked cupboards in a locked repository.

Electronic copies of data will be saved in password-protected files. All data will be backed up daily by the MLW Data Office onto a physical server, and then via internet to a cloud-based server.

### **11.5. Quality assurance**

Data will be checked for internal inconsistencies during verification and following data entry. Quality assurance protocols are in place for each stage of the study, as detailed in the individual SOPs.

For the Electronic TB Database, records will be periodically checked for completeness against Paper TB Registers, and by random selection of patients for home visit to provide ongoing QA/QC of the routinely collected TB data.

## 12. ADVERSE EVENT MONITORING AND REPORTING

**The intervention has minimal potential for harm**, with all components already conforming to International Best Practice: rather the research component relates to the impact evaluation through prevalence survey and skin testing of a public health intervention.

- Both systematic screening for TB and HIV self-testing are recommended by the WHO as International Best Practice for high HIV and TB prevalence settings, with urban Blantyre meeting both TB and HIV epidemiological criteria for community-based interventions
- Malawi National TB programme policy specifically endorses ACF in urban settings. Because of the limited sensitivity of all available TB screening tools in PLHIV, there is no single recommended screening algorithm, and the one proposed here (symptoms-then-microscopy) is one of the internationally recognised options for community-based ACF.
- Malawi National HIV Policy specifically endorses HIV self-testing in communities with high prevalence of undiagnosed HIV
- Malawi National HIV Policy specifically recommends urine LF-LAM for diagnosis of TB in symptomatic PLHIV, including outpatients

**The main trial outcomes will not be available** until the results of the post-intervention prevalence survey is completed, and so there is no basis from which to recommend early termination of the intervention.

As such, **we request exception from a formal Data Safety and Monitoring Board (DSMB)**, as being not indicated. The trial will instead be managed by periodic reports of progress and reporting all identified anticipated harms to a Trial Steering Committee (TSC), the Ethics Committees, and the MLW Community Advisory Group.

### 12.1. Anticipated harms from the intervention

Although minimal, risks from TB screening include potential for false positive and false negative HIV and TB results, and (41). These will be minimized by meticulous QA of microscopy results (blinded double reading of positives and a selection of negative smears), and by providing confirmatory testing of all provisionally smear-positive or LF-LAM positive participants.

Oral HIV self-testing is highly accurate when supported by brief in person demonstration and has a well-established strong safety record reported from Malawi (8, 36,37). No suicides have been reported from over a million self-tests in Southern Africa. The ACF team members will be trained to provide HIV self-testing in a safe, accurate and supportive way, using methods that are well established within MLW and Malawi. This will include basic psychological support and how to facilitate treatment of positive TB or HIV results (36).

### 12.2. Institutional responsibilities

Adverse events will be reported immediately to the Principal Investigator and will be logged and reported through regular follow-up reports.

A 6-monthly progress report will report on safety as well as other important process indicators and will be sent to the Trial Steering Committee Members, Ethics Committees, and collaborators in Ministry of Health of Malawi and Blantyre District Health Office.

### 12.3. Reporting Procedures

Adverse event forms will be completed by the Trial Coordinator and reported to the Principal Investigator. The Principal Investigator will check the form, make changes as necessary, sign and email a scanned copy of the form to the Ethics Committees and Sponsor.

In all cases participants experiencing adverse events will be followed up until final clinical outcome has been established (complete clinical recovery, or clinical condition has stabilised).

Adverse events will be evaluated for seriousness, and likely causality by the Principal Investigator for final classification.

The following adverse events will be systematically recorded and reported, while recognising that complete capture cannot be guaranteed during this type of public-health intervention:

- Misclassification or misinterpretation of results reported in error to a participant or their medical team, and with potential to result in TB or HIV treatment being started in error
- Serious adverse events relating to HIV self-testing, as previously defined by MLW and WHO (37)
- Withdrawal from further investigations by a participant with untreated positive sputum microbiology

#### **12.4. Good Clinical Practice (GCP)**

The principles of GCP will be adhered to throughout, and all research staff will have certified GCP training and will adhere to ICH-GCP requirements for source documentation and storage.

For the routinely-captured TB programme data, documentation to ICH-GCP standards will not be possible, and nor will written informed consent for data capture. Instead, Routine District Health Office TB Officers will be provided with protocol and modified GCP training. An established programmatic quality assurance/quality control (QA/QC) SOP will be used to maintain and understand data quality, with a verbal consent process for use of data and possible home visit for QA/QC purposes built into the Electronic TB Register.

#### **12.5. Monitoring and audit**

Project managers and supervisors will be responsible for day-to-day monitoring. Project meetings attended by all field staff will be held each fortnight, during which any problems encountered problems will be discussed and refresher training will be provided.

Internal audits will be conducted within 3 months of starting the intervention, and not less than annually during the intervention stage. These will include audit of study documentation, data storage, protocol adherence and SAE and incident reporting. A report will be circulated among TSC members and project managers. [name] will responsible for ensuring that problem areas identified during the audits are rectified, and for circulating details of actions taken to the TSC.

The LSHTM, College of Medicine Research Support Centre and MLW Research Governance Officer may carry out external audit of this study, but otherwise, no external audit will be carried out.

### 13. ECONOMIC EVALUATION

The main objective of the economic evaluation is to estimate the affordability and cost-effectiveness of the TB/HIV ACF intervention with the main focus being the TB intervention.

Specifically, we will estimate the incremental cost-effectiveness of ACF in comparison to facility-based case-finding only. To achieve this, inputs (costs) and outputs will be estimated.

Effectiveness data will be provided by:

1. Numbers of additional patients started on TB treatment, both a) following detection of undiagnosed patients by the ACF and b) as evidenced by differences between trial arms in notification rates identified through the Blantyre District Electronic TB Register (“additionality”)
2. Numbers of **new TB cases** and **TB deaths** averted as estimated from fitting an established HIV and TB model (13) to pre-intervention and post-intervention survey data and case-notifications.

Key outputs will be:

1. Incremental costs per additional individual started on TB treatment (using both direct diagnosis by the ACF team and additionality capture by the Electronic TB Register)
2. Incremental costs per DALY, new TB case, new TB infection and TB death averted

Two economic evaluations will be undertaken: firstly, a within trial evaluation; and secondly, projection a fully-costed dynamic transmission model. Both will be used to estimate the expected incremental cost per disability-adjusted life year (DALY). The mathematical model will estimate TB infection, case and TB death averted. For each analyses, the perspective will be that of the provider, and will only include the direct intervention and medical costs.

The within trial evaluation will adopt a time horizon matching the length of intervention in the trial, with no need to discount costs or DALYs given that the intervention is brief. The model-based evaluation will adopt a 20 year horizon, with future costs and DALYs discounted at 3.5%, and sensitivity analysis to explore alternative discount rates.

The primary analysis will focus on the direct intervention and the broader healthcare costs. This will include the costs of TB and HIV screening, the costs incurred in linking participants to TB/HIV services and any associated staff costs.

The healthcare resources used will be captured prospectively and primary costing studies will be undertaken to estimate the unit costs for these identified resources. The broader healthcare resource use will be captured through interview of patients who are SCALE cluster residents (both intervention and non-intervention arms) starting TB treatment at routine facilities.

The provider-costs of treating TB will be estimated from previously collected inpatient data (43,44) and from interview of TB outpatients and District Health staff to establish:

- Outpatient clinic visits
- Days of inpatient hospital care
- Medications
- Investigations and procedures

As Malawi Ministry of Health does not have reference costs for these healthcare resources, previous unit costs estimated in Malawi will be used to derive total costs.

Mean costs and outcomes for the ACF model used in SCALE will be estimated, together with the mean incremental cost-effectiveness ratio. Measures of uncertainty (standard errors and confidence intervals) will also be reported for the mean estimates.

Sensitivity and scenario analysis will also be considered. This will include undertaking a cost-effectiveness analysis where the primary outcome will reflect two outcomes being evaluated in the trial: the proportion of participants with undiagnosed or untreated TB. As missing data is a common occurrence in trials, additional analysis will explore impact of missing data and alternative approaches to account for missing data.

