| 4. Economic and mathematical modelling analyses | 
4.1 to determine the costs
 
 
per adult screened with microscopy during ACF
 
per smear+ve TB patient detected by the ACF team
 
per additional adult investigated for TB by the routine health system
 
per additional adult diagnosed with TB by the routine health system
 
likely final scale-up programme costs
 
 
4.2 to determine the incremental costs of adding HIV to TB ACF
 
 
per adult screened for HIV by the ACF team
 
per adult with HIV detected by the ACF team
 
per adult started on ART
 
 
4.3 to estimate the cost-effectiveness per new TB infection, TB case, and TB death averted by TB and TB+HIV ACF
 | 
4.1 Costing of ACF from the provider-perspective. Denominators will use records from the ACF team, and routine health system data collected by trial arm under the extended TB surveillance system.
 
4.2 Costing of HIV self-testing HIV-positive clients to the TB-ACF, with denominators obtained from ACF team and facility records
 
4.3 Fully costed mathematical modelling of the TB-ACF intervention with and without additional HIV testing components.
 |

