#### 7.1.2. Enhanced surveillance of routinely diagnosed TB patients in Blantyre

In collaboration with Blantyre District Health Office (DHO), place of residence (GPS coordinates) and national TB programme data will be collected on all (~2,500 per year) TB

patients into an electronic database, together with a sputum specimen for TB microscopy and culture.

These Electronic TB Register records will be used to assign cluster-resident status (yes/no; cluster number and trial arm) for all registering TB patients during this trial, allowing cluster-level TB case-notification rates to be calculated.

For the purposes of this protocol, MLW will work with Blantyre DHO to adapt the current paper-based Presumptive TB Register, used to record patients being investigated for TB and the results of microbiological tests, into an Electronic Register that allows place of residence GPS coordinates to be captured, enabling investigation of cluster-level rates of TB investigations at primary care level (Appendix 4.3a&b Consent, Appendix 4.5a&b Patient Information Sheet and Appendix 4.4 CRF). MLW will also work with Chiradzulu DHO to add Chiradzulu District Hospital to the Electronic Register, since it has been identified that approximately 34% of patients who registered for TB treatment there in 2017-2019 came from the Blantyre urban area.

Qualitative in-depth interviews will be carried out with purposively selected patients being investigated for TB at primary care level because of cough, aiming to identify cues to action (Appendix 4.1a&b Consent forms, Appendix 4.6a&b participant information sheets and Appendix 4.8 topic guide).

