Results of sputum microscopy will be delivered back to participants at a pre-defined results collection point 2 to 4 working days after collection. Participants with positive smears who do not attend for results collection will be visited at home.

All participants with positive TB results will be assisted or accompanied to attend the nearest TB registration centre for treatment registration (Appendix 2.5 TB referral form).

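### Section 13 uses ACF-team detections in an incremental cost ratio although they have no standard-of-care comparison and overlap the between-arm register difference

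*Combined protocol and SAP*

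**What the plan says.** Section 13 states its question as follows: "we will estimate the incremental cost-effectiveness of ACF in comparison to facility-based case-finding only". Its first effectiveness input is a count of people put on treatment whom it labels additional, identified in two ways: "both a) following detection of undiagnosed patients by the ACF and b) as evidenced by differences between trial arms in notification rates" in the Electronic TB Register. The term additionality is attached to the second of these. The first key output then draws on the two together: "Incremental costs per additional individual started on TB treatment (using both direct diagnosis by the ACF team and additionality capture" by that register.

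Call the ACF-detected patients who start treatment count (a), and the between-arm register difference count (b). Three other places fix how they relate:

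- Section 10.4.2: "All participants with positive TB results will be assisted or accompanied to attend the nearest TB registration centre for treatment registration".
- Section 7.1.2: "These Electronic TB Register records will be used to assign cluster-resident status (yes/no; cluster number and trial arm) for all registering TB patients".
- Section 9.3.3: a positive smear or Xpert result counts whether it came from a routine or a research laboratory.

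The synopsis (Section 4, item 4.1) separately lists a cost "per smear+ve TB patient detected by the ACF team", alongside a cost per additional adult diagnosed by the routine health system. Section 14.2 defers the detailed statistical analysis plan, so nothing later in the document settles the matter.

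**The concern.** An incremental ratio divides the extra cost of ACF by the extra patients treated compared with what would have happened without it. In this trial the randomised SOC arm supplies that counterfactual. Count (a) does not use it: a patient who gave sputum to the ACF team but would have been diagnosed at a clinic in the same window is still counted as additional.

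The two counts also overlap, and Section 13 has no rule for combining them. A cost per additional patient could therefore be published with a denominator that is not incremental, or that contains some patients twice. It is the first-listed key output of an evaluation intended to inform wider implementation. The primary comparison of notification rates is not affected.

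**Working it through.** The documents give no figure for additional patients or for cost per additional patient, so there is nothing to reproduce. The check has two parts.

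**1. Overlap, from the text.** An ACF-positive participant is helped to a TB registration centre (10.4.2). The register assigns cluster and arm to every registrant (7.1.2), and a positive result is accepted from any source (9.3.3). No rule removes ACF-found patients. Each one who registers as a cluster resident therefore adds one to the ACF-arm numerator of (b). Section 6.1 agrees: its first research question treats direct ACF diagnosis as one possible component of increased notifications.

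**2. Size, as an illustration.**

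Inputs:
- Adults per arm: 150,000 (14.1).
- Undiagnosed TB: 200 per 100,000 (5.1.1, initial results of the pre-intervention survey).
- Share of undiagnosed cases found per round: 20-25% (5.2.1, from Harare).
- SOC notification rate, microbiologically-confirmed TB: 70-100 per 100,000 per year (14.1).
- f, the share of ACF-found patients who would not otherwise have registered in the window: not in the documents, ranged 0 to 1.
- Wider behaviour effect: set to zero.

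Count (a) = 150,000 × 200/100,000 × 0.20 to 0.25 = 300 × 0.20 to 0.25 = **60 to 75**.

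Expected SOC notifications = 150,000 × 70 to 100 per 100,000 = 105 to 150 over 12 months, or 26 to 38 over 3 months.

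True additional number: b = f × a. Sum: a + b = (1 + f) × a. Overstatement by the sum: (a + b)/b = (1 + f)/f.

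| f | (b), true additional | (a) alone | a + b | (a + b)/b |
|---|---|---|---|---|
| 0 | 0 | 60-75 | 60-75 | undefined |
| 0.25 | 15-19 | 60-75 | 75-94 | 5.0 |
| 0.5 | 30-38 | 60-75 | 90-113 | 3.0 |
| 1 | 60-75 | 60-75 | 120-150 | 2.0 |

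For a given incremental cost, the sum understates the cost per additional patient by the factor in the last column. Using (a) alone gives f times the correct cost: half of it at f = 0.5, and the correct value at f = 1.

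**Limits on f.** Displaced patients, (1 − f) × a, cannot exceed the notifications expected without ACF, N. So f ≥ 1 − N/a if all of (a) register in the window.
- 12 months: N = 105-150 exceeds (a), so f = 0 is arithmetically possible. It would need 60/150 = 40% to 75/105 = 71% of expected notifications to be displaced, which is extreme.
- 3 months: f is at least 1 − 37.5/60 = 0.375 (a = 60, rate 100) to 1 − 26.25/75 = 0.65 (a = 75, rate 70). The overstatement by the sum then lies between 2.0 and 1.375/0.375 = 3.7.

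**Behaviour effect.** If ACF also prompts w extra clinic diagnoses, b = f × a + w and the overstatement is 1 + a/b, which is smaller. For f = 1 and w = a it is 1 + a/(2a) = 1.5. In that case (a) alone would be too small, not too large.

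**The case against.** The strongest reply is that Section 13 never says the counts are added. Its wording fits two data sources or two reported ratios. The synopsis keeps ACF-detected patients and additional routine diagnoses apart, and Section 6.1 shows that the investigators see direct diagnosis as part of the notification increase. This stands: summation is one reading only, and the text elsewhere leans towards separate reporting. It does not remove the problem. Reported separately, the (a) ratio still carries the words incremental and additional without a comparator. The synopsis split is also not the split in Section 13, where (b) covers all registrants and not only routine diagnoses.

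A reader might go further and infer that the evaluation would credit ACF with extra patients whatever the trial showed. The documents do not support that. Count (b) is named in the same sentence, is a randomised comparison, is zero in expectation if ACF has no effect, and can be negative. Nor is it supported that everyone the ACF team finds is counted, since (a) is confined to those who start treatment. It would also be wrong to combine no effect with 60-75 registered ACF patients over 3 months: only 26-38 notifications are expected in that time, so (b) would be clearly positive.

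Finally, this is one output of a secondary evaluation, and DALY-based, model-based and sensitivity analyses are also planned. That limits the weight of the point.

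**Conclusion.** The point holds in a limited form. Count (a) is called additional and used in an incremental ratio without an SOC counterfactual, contrary to the section's own comparator. Its registered patients are already inside (b), and the plan is silent on how the two are combined. If they are shown separately, the fault is one of labelling: an average cost per ACF-detected patient presented as incremental. If they are summed, the denominator is about twice the true value when every ACF-found patient is truly additional and three times when half are.

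These factors assume no wider behaviour effect and that all ACF-found patients who start treatment register in the window. They depend on f, which the documents do not give. The counts of 60-75 rest on a detection share from another city applied to interim survey results; the factors do not depend on them, although the feasible range of f does. The wording should be corrected before the economic analysis. The primary outcome is untouched.

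**What to change.** In Section 13 and the economic analysis plan:

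1. Use the between-arm register difference (b) alone as the denominator of the incremental cost ratio, and delete the reference to direct diagnosis by the ACF team from key output 1.
2. Report (a) only as a yield measure, the cost per ACF-detected patient started on treatment, next to the unit cost already in the synopsis. Do not call it additional or incremental, and do not add it to (b).
3. State which register endpoint (b) uses: all patients started on treatment, or microbiologically-confirmed TB only. Section 13 speaks of starting treatment without restriction, whereas the primary outcome is restricted, so taking over the primary estimate unchanged would silently drop clinically diagnosed patients.
4. State the window for (b), consistent with the within-trial horizon, which Section 13 sets to the length of the intervention. The primary-outcome window cannot simply be borrowed: it is 3 months in the Section 9.1 text and 12 months in the table that follows.

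This is a change of wording and uses data already planned. The price is a less precise ratio, which may be less favourable and is undefined if the arms do not differ. In that case, give the incremental cost and the incremental number of patients separately, with their intervals.
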